### Criteria for discontinuing or modifying allocated interventions {11b}

A clinical committee may decide to modify the treatment regimen to start an individualised regimen in patients with specific problems. The most common situations for which the regimen may be discontinued include :Results of baseline DST may not be available before the start of treatment. If resistance to components of the treatment regimen is reported after the start of treatment it may be necessary to modify the treatment regimen taking into account DST results.Grade 3 or higher toxicity may lead to the temporary or permanent suspension of one or more drugs, which then may need to be replaced.Treatment failure (see the “Definition” section). In such patients, a new RR-TB treatment regimen is warranted. For the control arm, 4-6 Lzd-Hh-Bdq-Dlm-Cfz-Z/5 Bdq-Dlm-Cfz-Z will be used as re-treatment RR-TB regimen. For the experimental arm, the composition will be based on DST. The evaluation of re-treatment outcomes is not part of this study.

In patients with renal insufficiency the regimen is adapted as follows:If renal failure is present before the start of treatment, the SLID is replaced with LZD (similar approach as when audiometry abnormalities are present) and pyrazinamide is administered thrice weekly instead of daily.If during treatment with SLID the creatinine clearance is less than 90 ml/min, the SLID is prescribed twice or thrice weekly at 12–15 mg/kg; and ethambutol and pyrazinamide are given thrice weekly. If creatinine clearance is less than 60 ml/min the SLID will be replaced with LZD, while ethambutol and pyrazinamide are administered 3 times a week instead of daily.

Safety data collected during treatment with either the control or experimental regimen will be included in the safety analysis. Effectiveness data will be used from all patients enrolled on RR-TB treatment. However, if the regimen was changed during treatment to better fit the initial resistance pattern, such a patient will be excluded from the effectiveness analysis, as the patient had a contra-indication for the study regimen (see the exclusion criteria).

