### Participant timeline {13}

Depending of the month of RR-TB diagnosis, as shown on the printed Xpert MTB/RIF result, the patient is enrolled on either the control or experimental treatment arm (a coin toss determines which regimen is used for which month). Each patient is treated for 9 to 11 months and is followed actively for 12 months after the end of treatment.

The inclusion assessment includes clinical, bacteriological, laboratory and additional tests described in Table 1.

**Table 1 Tab1:** Enrolment and assessments

		Enrolment	Treatment phase (M = month)											Follow-up		Close-out
			M 1	M 2	M 3	M 4	M 5	M 6	M 7	M 8	M 9	M 10	M 11	MF 6	MF 12	
Eligibility screening		X														
Written informed consent		X														
Allocation		X														
Assessment	Clinical examination	X	X	X	X	X	X	X	X	X	X	X*	X*	X	X	
	Treatment adherence		X	X	X	X	X	X	X	X	X	X*	X*			
	Sputum smear	X (2)	X	X	X	X (2)	X (2)*	X (2)*	X	X	X (2)	X(2)*	X (2)*	X	X	
	Bacteriological culture	X		X		X		X			X	X*	X*	X	X	
	SL-LPA (FQ/Injectables)	X												X±	X±	
	Haemoglobin/CBC#, creatinine@, potassium@, liver enzymes	X	X	X	X	X	X*	X*								
	Visual acuity, test for peripheral neuropathy, Audiometry@	X	X	X	X	X*	X*									
	Chest X-ray	X									X	X*	X*			
	ECG§	X		X		X		X		X		X*	X*			
Safety outcome evaluation													X	X		
Treatment outcome evaluation																X

*If the intensive phase is prolonged

**±** DST carried out at baseline, after reversion (positive culture after conversion) during treatment, and if bacteriological culture is positive during the 12-month post-treatment follow-up (with storage of the baseline, treatment failure or relapse strain for genotypic analysis)

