# To be done if the patient is taking linezolid

@ To be done if the patient is taking a second-line injectable drug

**§** A basic electrocardiogram (ECG) must be performed and additional ECGs done at weeks 1 and 2 after the start of treatment and then once a month during treatment. The ECGs must be repeated if necessary in the event of clinical suspicion of heart rhythm problems and conduction disorders, or other clinical signs (e.g. dehydration and electrolyte disorders)

Abbreviations: *CBC* complete blood count, *ECG* electrocardiogram, *FQ* fluoroquinolone, *M* month, *MF* month of follow-up after treatment completion, *SL-LPA* second-line line probe assay

Baseline sputum samples are systematically sent to the NRL and the ITM in Antwerp. However, as in any life-saving situation, treatment of drug-resistant tuberculosis is not withheld from a patient when DST results are not available. Hence the regimen may be modified once DST results become available {see 11b}.

All patients enrolled in the study undergo regular assessment of clinical and para-clinical parameters as described in Table 1. Monitoring procedures are adapted to fit the drugs used in either the control or experimental treatment arm (e.g. close monitoring of haemoglobin for patients taking LZD; monthly audiometry when a SLID is used).

Before starting treatment with linezolid, providers invite family members to collect blood bags to be able to do a timely blood transfusion in the event of bone marrow aplasia.

Every month sputum samples are collected for bacteriological monitoring using smear microscopy with auramine staining. In case of lack of conversion on smear microscopy at month four (two samples), the intensive phase is extended for one or 2 months maximally.

At month two, four, six and nine (10 or 11 if the intensive phase was prolonged with 1 or 2 months, respectively), samples are collected for culture. Post-treatment follow-up at 6 and 12 months after cure or treatment completion relies on smear microscopy and culture.

In the event of a treatment failure during treatment or relapse during the 12-month post-treatment follow-up, genotyping is done at the ITM in Antwerp on the baseline and failure/relapse sample to determine the strain identify and to distinguish between true treatment failure/relapse and reinfection.

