## Data collection and management

### Plans for assessment and collection of outcomes {18a}

Safety: Patients will be screened monthly by a person trained in the diagnosis and management of AE.

During the inclusion visit, pathologies associated with a high risk of adverse effects such as diabetes, kidney and liver failure, malnutrition, HIV infection, alcohol and drug abuse, etc. should be identified and recorded. The underlying causes of adverse effects will be identified and treated.

AE are classified according to their severity using ARNS scale (Table 2) and noted in the patient’s file.

**Table 2 Tab2:** Severity rating of adverse effects

Degree	Description
Degree 1: Slight abnormality	Mild or transient discomfort, without limitation of usual daily activity; does not require medical intervention or corrective treatment.
Grade 2: Moderate abnormality	Partial limitation of usual daily activity; medical intervention or corrective treatment required. No need to interrupt treatment.
Grade 3: Severe abnormality	Limitation of usual daily activity; requires medical intervention and corrective treatment, possible hospitalisation. It may be necessary to stop the responsible medication temporarily until the symptoms disappear.
Grade 4: Life threatening or permanent injury	Very limited activity; requiring medical intervention and corrective treatment, almost always in a hospital environment. It may be necessary to stop the responsible drug permanently.
Grade 5: Death	

Grade 1 adverse events will only be recorded in the patient's file without further action; those of grade 2 often require a medical intervention with auxiliary drugs

Any grade 3–5 AE are classified as severe AE

All AE will be reported in the patient treatment card. When an AE occurs, the investigator responsible for the care of the patient will first assess and grade the event. If it is graded 4–5, or if other serious AE (SAE) criteria (such as hospitalisation) apply, then a “severe AE form” will be completed and sent to the principal investigator and the relevant pharmacovigilance authority (Fig.1).

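### Kidney failure is to be identified at inclusion in both arms, but the only renal test in Table 1 is conditional on an injectable that the experimental regimen does not contain

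*Protocol article*

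**What the plan says.** Four places in the protocol article bear on this.

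- **Criteria for discontinuing or modifying allocated interventions {11b}.** The regimen is adapted in patients with renal insufficiency. The first limb applies before treatment: "If renal failure is present before the start of treatment, the SLID is replaced with LZD", and "pyrazinamide is administered thrice weekly instead of daily". Two further limbs apply on treatment: "If during treatment with SLID the creatinine clearance is less than 90 ml/min", the injectable, ethambutol and pyrazinamide are given less often; and "If creatinine clearance is less than 60 ml/min the SLID will be replaced with LZD", with ethambutol and pyrazinamide again on a reduced schedule.
- **Plans for assessment and collection of outcomes {18a}.** At the inclusion visit the staff are to identify and record "pathologies associated with a high risk of adverse effects such as diabetes, kidney and liver failure", among other conditions. No arm is singled out and no test is named.
- **Participant timeline {13}.** "The inclusion assessment includes clinical, bacteriological, laboratory and additional tests described in Table 1". The relevant row of Table 1 is "Haemoglobin/CBC#, creatinine@, potassium@, liver enzymes", marked at Enrolment and months 1 to 4, and at months 5 and 6 if the intensive phase is prolonged.
- **Table 1, footnote @**, attached to creatinine, potassium and audiometry: "To be done if the patient is taking a second-line injectable drug".

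The interventions section {6b, 11a} puts pyrazinamide in both regimens throughout. The experimental regimen contains no injectable.

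**The concern.** A written safety adaptation needs an input. Here the text asks for renal failure to be recognised before treatment in patients of either arm, while the assessment schedule ties the only renal measurement to a drug that one arm does not use. If sites follow the footnote, baseline renal failure in the experimental arm would be recognised only from history or symptoms, whereas control patients would have a laboratory value.

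Two things are at stake. The first is patient safety: the pre-treatment adaptation of pyrazinamide may not be applied where the text appears to call for it. The second is comparability: a baseline condition that the protocol itself lists as raising the risk of adverse effects would be ascertained differently by arm, in a trial whose primary endpoint is grade 3–5 adverse events.

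**Working it through.** There is no figure to recompute. The check sets each limb of the renal rule against the schedule.

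1. **Before treatment, control patients due to receive the injectable.** Creatinine has an Enrolment mark. Taken literally, footnote @ cancels it, because nobody is taking an injectable at enrolment. Audiometry carries the same footnote, yet the Background and the Discussion say it is done at baseline, and the interventions section uses the baseline result to decide whether linezolid replaces the injectable. The footnote must therefore mean something like due to receive or receiving. On that reading the measurement exists and only the wording is at fault.

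2. **Before treatment, experimental patients.** Allocation follows the month of diagnosis and is known when the patient reaches the clinic (sections {16a} and {16b}). Staff thus know at enrolment that no injectable is due. The generous reading from step 1 then confirms that creatinine is not scheduled for these patients, at Enrolment or in any other column. Liver enzymes, in the same row, carry no footnote. Of the two organ failures that {18a} names together, one has an unconditional test and the other does not.

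3. **Does the rule reach the experimental arm?** The part about replacing the injectable cannot. The part about pyrazinamide can, since pyrazinamide is in that regimen and the rule is introduced for patients with renal insufficiency without naming an arm. The inclusion-visit requirement in {18a} is not restricted by arm either.

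4. **During injectable treatment.** The limb for clearance below 90 ml/min is expressly confined to this period. The limb below 60 ml/min replaces the injectable, so the patient must still be on it. Creatinine is scheduled monthly over the same months. Trigger and measurement match.

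5. **After a switch to linezolid.** {11b} states no further clearance trigger, so no stated trigger lacks its input. The altered ethambutol and pyrazinamide schedule does continue, because both drugs run throughout the control regimen. Read as written, footnote @ stops creatinine on the day of the switch.

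The gap that remains is step 2, with a wording problem in step 1 and an unclear point in step 5.

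**The case against.** The strongest reply is that the renal rule is written for the control arm. Its first action is to replace the injectable, which has no meaning elsewhere, and both clearance limbs presuppose an injectable. The participant-timeline section says monitoring is fitted to the drugs used, so tying kidney tests to the injectable is deliberate. {18a} already asks for kidney failure to be identified, monitoring may be intensified when a patient presents with a problem, and adverse events are followed until they resolve or stabilise.

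Much of this stands. A reader might infer that creatinine is measured only once the injectable has begun, so that the control-arm decision is circular; the Enrolment mark and the baseline audiometry under the same footnote do not support that. A reader might also infer that the rule goes on operating without data after the injectable stops, or later in the experimental arm; {11b} states no trigger for either situation. Nor do the documents support saying that all 115 experimental patients are affected, or that some given share of control patients is.

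What does not stand is the claim that the gap is filled elsewhere. Unscheduled examinations respond to a presenting problem and are not an inclusion screen. {18a} states the requirement but names no test, and the inclusion assessment refers to Table 1 for its tests. If the renal rule is meant for the control arm alone, the text does not say so, and its pyrazinamide limb reads otherwise.

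**Conclusion.** The point holds in a narrow form. The requirement to identify kidney failure at inclusion and the pre-treatment pyrazinamide limb are not limited by arm, while the only scheduled renal test is limited to patients on, or at best due for, an injectable. This leaves the experimental arm, 115 planned patients, without a scheduled creatinine at enrolment. Control patients placed on linezolid from the outset may be in the same position, depending on how the footnote is read.

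The 115 is the number without the scheduled test, not the number harmed. Only patients with renal failure before treatment could miss the adaptation, and the protocol gives no frequency for that. The conclusion assumes that sites apply footnote @ as printed and that the renal rule is meant to cover any patient taking pyrazinamide. If the second assumption is wrong, the defect is an unstated scope rather than a missing test, and the text still needs correcting. The lack of scheduled creatinine after a switch is secondary.

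**What to change.** Reconcile {11b}, {18a} and footnote @ of Table 1 in one of two ways:

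- word the footnote so that the enrolment creatinine is not conditional on the injectable; or
- state in {11b} and {18a} which patients the renal rule covers, and how renal failure is identified in those for whom no creatinine is scheduled.

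Under either option, reword the footnote so that the Enrolment mark makes sense for control patients who have not yet started the injectable, and say whether creatinine is meant to end when the injectable is replaced while the adapted schedule continues. Which option is right, and any dosing, is for the clinical team.

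The cost is a few lines of text and, under the first option, at most one routine creatinine per patient at a visit that already schedules blood for liver enzymes.

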### Outcomes {12}

Primary endpoint, as a measure of safety: any severe (grade 3–5) AE, with onset of symptoms before the end of treatment, and with the maximum grade measured up to 6 months after the end of treatment.

Secondary endpoints:As a measure of effectiveness: treatment outcome, with relapse-free success (cure or treatment completion without proof of relapse during 12 months of active post-treatment follow-up) as favourable outcome and treatment failure, relapse, lost to follow-up, and death as an unfavourable outcome.As a measure of adherence to the regimen: proportion of daily doses taken.

The definitions used to grade AE are based on French National Agency for Research on AIDS and hepatitis (ANRS) [19].

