Effectiveness: Outcomes will be assessed during treatment and, in case of cure or treatment completion, at the end of 12 months post-treatment follow-up

*Therapeutic success*: Composite result corresponding to the combination of “cured” + “treatment completed” (= treatment success) without relapse during the 12-month follow-up period

Note: this result can also be defined as “recovery without relapse”.

*Cured*: A patient with bacteriologically confirmed RR-TB who has completed 9-11 months of treatment without evidence of treatment failure AND at least 2 consecutive cultures at least 30 days apart are negative in the continuation phase and not followed by a positive culture result during treatment and post-treatment follow-up.

*Treatment completed*: A patient who has completed 9 to 11 months of treatment with the regimen with no evidence of treatment failure BUT not fulfilling the definition of “cured”.

*Treatment failure*: The treatment is interrupted or it is necessary to permanently change the treatment regimen of at least two anti-tuberculosis drugs due to:A lack of bacteriological conversion of sputum after 6 months of treatment, orA reversion of the sputum bacteriological culture after 7 months of treatment in a patient with a previously negative culture, orEvidence of additional drug resistance acquired in the treatment regimen of the study in patients with either treatment failure or relapse, and without proof of a between baseline and recurrence genotypically different strain, orAE leading to the modification of at least two anti-TB drugs in the treatment regimen

*Deceased*: A patient who has died during treatment from any cause.

*Lost to follow-up:* A patient whose treatment has been interrupted for 2 or more consecutive months.

*Not evaluated*: A patient for whom no treatment outcome is assigned (this includes cases “transferred out of the study area” to another treatment unit and whose treatment outcome is unknown or cannot be assessed)

*Relapse:* A patient who has been treated for RR-TB, has been declared “cured” or “treatment completed” and is diagnosed with another episode of confirmed RR-TB with rifampicin-resistant bacilli, within one-year follow-up, and without proof of a between baseline and recurrence genotypically different strain.

*Reinfection:* Recurrence (treatment failure or relapse) with proof of a between baseline and recurrence genotypically different strain.

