*Withdrawn*: A patient is withdrawn from treatment for a reason other than treatment failure (e.g. resistance to second-line basic drugs, the patient’s informed consent is withdrawn or other reasons) and referred back to the standard treatment programme for routine care.

For the purpose of the effectiveness analysis, relapse-free success will be the favourable outcome. Unfavourable outcomes include death, failure, lost to follow-up during treatment and relapse (patients withdrawn will be excluded).

Adherence: Adherence will be assessed by the number of patients who are receiving the experimental treatment arm among all eligible patients, compared to the number of patients on the control treatment arm. Patients are considered adherent when 90% of the treatment doses were taken. Adherence is assessed based on the information on the treatment cards, measured over the total treatment period.

*Processing time*: The cumulative delay between sample collection and the start of RR-TB treatment.

*Registration rate:* The number of patients who started treatment among those with confirmed RR-TB.

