#### Secondary analysis

By treatment arm, safety will be calculated as the proportion of all patients started on treatment and without any severe AE (safety endpoint). By treatment arm, treatment effectiveness will be calculated as the proportion of patients with a favourable outcome among all patients with either a favourable or unfavourable outcome. By treatment arm, adherence will be calculated as the proportion of patients who took at least 90% of the doses of RR-TB treatment. Cohorts will be compared using the chi-squared test. Bivariable and multivariable logistic regression models will be used to estimate the association between having an unfavourable treatment outcome and treatment arm (experimental vs control; the variable of interest), adjusted for potential confounding factors such as age, sex, HIV status, type of tuberculosis, bacillary load, extent of disease, body mass index (BMI) and initial resistance pattern. Factors associated (*p*-value <0.1) with having an unfavourable outcome will be included in the multivariable model, which then will be simplified by backwards elimination until all remaining factors have a *p*-value <0.05 (treatment arm, the variable of interest, will not be removed).

An additional Cox regression model will be developed to estimate the association between the variable “exposure to SLID vs LZD” and having a grade 3–5 AE probably or definitively related to either the SLID (ototoxicity) or LZD (haematological disorders, optic neuritis, neurological disorders). The variable “exposure to the injectable vs linezolid” will be treated as a time-dependent covariate, as described previously [15].

Analyses will be carried out with Stata software (version 16.1, College Station, TX).

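### Secondary effectiveness endpoint: outcome definitions can let post-treatment death or loss count as relapse-free success, and exclusions made after treatment start can differ by arm

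*Protocol article*

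**What the plan says.** All references are to the protocol article.

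- **Outcomes {12}.** The favourable outcome is "cure or treatment completion without proof of relapse during 12 months of active post-treatment follow-up". The section then gives "treatment failure, relapse, lost to follow-up, and death as an unfavourable outcome", with no time limit on death or loss.
- **Plans for assessment and collection of outcomes {18a}.** Therapeutic success is cure or completion "without relapse during the 12-month follow-up period". *Deceased* is "A patient who has died during treatment from any cause". *Lost to follow-up* is "A patient whose treatment has been interrupted for 2 or more consecutive months". The list of unfavourable outcomes for the analysis names death and failure, then "lost to follow-up during treatment and relapse (patients withdrawn will be excluded". The reasons given for *Withdrawn* include resistance, withdrawn consent and an open category of other reasons.
- **Methods for additional analyses {20b}{20c}.** The only rule for losses concerns those during treatment.
- **Criteria for discontinuing or modifying allocated interventions {11b}.** Effectiveness data are to come from everyone enrolled on treatment, but "if the regimen was changed during treatment to better fit the initial resistance pattern, such a patient will be excluded from the effectiveness analysis". The stated reason is a contraindication, with a pointer to the exclusion criteria.
- **Secondary analysis.** Effectiveness is "the proportion of patients with a favourable outcome among all patients with either a favourable or unfavourable outcome".

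**The concern.** There are two separate problems.

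First, relapse-free success a year after treatment should mean that the patient was alive and, as far as could be checked, free of disease. If death and loss stop counting when treatment ends, and success needs only the absence of proof of relapse, a patient who was never examined again can be recorded as a success. This raises the reported level in each arm. It distorts the comparison only if post-treatment death or loss differs between arms.

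Second, patients are removed after they have been allocated and treated, because of what was then done to their regimen. The two regimens contain different drugs, and clinicians, patients, researcher and statistician all know the arm. The patients left for analysis may therefore no longer be comparable.

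The trial is meant to inform Niger's treatment policy on effectiveness as well as safety. The Background section motivates it partly by a contrast of 73% against 83% success, so shifts of several points would matter to a reader.

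**Working it through.** **Plan figure.** The protocol states no sample size, power or margin for effectiveness. Its total of 230 belongs to the primary safety endpoint. With a hazard ratio of 3.2, two-sided alpha 0.05 and power 0.8, the Schoenfeld formula gives 23.2 events. Divided by the mean risk (5% + 15%)/2 = 10%, that is 232, close to 230. Nothing below depends on it.

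**Step 1: trace one patient through the definitions.** Take a patient who completes treatment and dies some months later with no relapse shown.

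- *Treatment failure*: no.
- *Deceased*: no, because death was not during treatment.
- *Lost to follow-up*: no, because treatment was not interrupted.
- *Relapse*: no.
- *Withdrawn*: no, because that means withdrawal from treatment.
- *Cured* or *treatment completed* without relapse: yes.

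Only the untimed mention of death in Outcomes {12}, and of death in the unfavourable list in {18a}, points the other way. A patient not seen after treatment follows the same path. Relapse is looked for by smear and culture at 6 and 12 months, so someone who does not attend is unlikely to yield proof of it.

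**Step 2: trace one baseline result through both arms.** The trigger in {11b} is reported resistance to components of the patient's regimen, after which a change may be made. Regimen contents are from {11a}.

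| Baseline resistance to | In control regimen | In experimental regimen | Possible exclusion |
|---|---|---|---|
| Second-line injectable | yes (unless replaced) | no | control only |
| Ethambutol | yes | no | control only |
| Bedaquiline | no | yes | experimental only |
| Fluoroquinolone | yes | yes | both |

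Table 1 schedules a baseline line probe assay for fluoroquinolones and injectables, so the first row rests on a routine test. Eligibility {10} names fluoroquinolone susceptibility as an inclusion condition. Its exclusions contain a general item on medical contraindications but no other named resistance.

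**Step 3: size of post-treatment death or loss (assumed rates).** The base is the 83% relapse-free cure cited in Background {6a}. If a share *l* of those counted as successes die or are lost after treatment, the overstatement is 0.83 × *l*.

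- *l* = 2%: 0.83 × 0.02 = 1.7 points
- *l* = 5%: 0.83 × 0.05 = 4.15 points
- *l* = 10%: 0.83 × 0.10 = 8.3 points

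The present rule would still report 83.0%. If the loss occurred in one arm only, an apparent difference of zero would hide the same number of points.

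**Step 4: size of a one-arm exclusion (assumed rates).** Let true success be 83% in both arms. A fraction *x* is removed from one arm, with success *s* among those removed. That arm then reports (0.83 − *x* × *s*)/(1 − *x*). For example, *x* = 10% and *s* = 40% gives (0.83 − 0.04)/0.90 = 87.8%.

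| *x* | *s* = 60% | *s* = 40% | *s* = 0% |
|---|---|---|---|
| 3% | 83.7% (+0.7) | 84.3% (+1.3) | 85.6% (+2.6) |
| 5% | 84.2% (+1.2) | 85.3% (+2.3) | 87.4% (+4.4) |
| 10% | 85.6% (+2.6) | 87.8% (+4.8) | 92.2% (+9.2) |

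Figures in brackets are the spurious difference in points. The formula holds for any removal, so it also covers withdrawn and not-evaluated patients. If those removed did better than 83%, the sign would reverse.

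**The case against.** **No sentence states that post-treatment deaths or losses are successes.** This is true. Death is listed without a time limit in Outcomes {12}, and in {18a} the words limiting the period follow loss, not death. Outcomes are assessed at the end of the 12 months, and *Not evaluated* could be read to cover a patient whose status is unknown, which would remove that patient from the denominator rather than make a success. So a reader might infer that the protocol plainly scores all such patients as favourable, and that goes too far. What stands is that the sections conflict, and that the defined terms lead to success.

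**Arm-dependence is an inference.** The exclusion wording is the same for both arms and the change is only possible, not required. The control strategy already allows linezolid to replace the injectable in some circumstances, and {11b} does not say how a swap for injectable resistance would be classed. Bedaquiline resistance would act in the opposite direction. A reader might infer that the rule favours a particular arm, but the documents support neither a direction nor a size.

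**The exclusion has some basis in eligibility.** The general contraindications item may be what {11b} points to. That is plausible, but the item does not define which baseline resistance counts.

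**Effectiveness is secondary and framed as descriptive.** This is correct. Sample size and interim stopping rest on grade 3–5 adverse events, and the primary analysis includes all patients who started treatment. It limits the weight of the point but does not remove it, because a chi-squared comparison and a multivariable model of effectiveness by arm are planned.

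**Sensitivity analyses may sit in an analysis plan that is not shown.** That may be so. The point here concerns rules that this document does state.

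**Conclusion.** The point holds for the secondary effectiveness endpoint. The definitions contradict each other on death and loss after treatment, and read together they can count such patients as relapse-free successes. This overstates the level of success, and it biases the comparison only if rates differ by arm. The exclusion after a resistance-driven change is discretionary and unblinded and can act in one arm only. Dropping withdrawn and not-evaluated patients opens the same route.

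On assumed rates and an 83% base, the first problem is worth about 1.7–8.3 points of level and the second about 0.7–9.2 points of difference, the top of the latter range requiring that none of the excluded patients succeed. The documents give no rate of post-treatment death, loss or exclusion, so these are ranges of what could happen, not estimates of bias. A reader might conclude that the comparison is shown to be biased or that the primary result is at risk. Neither is supported.

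**What to change.** 1. Reconcile Outcomes {12} with {18a} and {20b}{20c} so that death from any cause up to 12 months after treatment is unfavourable.
2. State that a patient without a month-12 status is not a verified success. Report effectiveness with these patients as unfavourable and also under the present rule, since counting every unknown as unfavourable is a convention with its own downward bias.
3. Define any resistance exclusion from the baseline DST result, identically in both arms and whether or not the regimen was changed. Name in the text which results count.
4. Analyse all other enrolled patients as allocated. This includes those not evaluated and those withdrawn for reasons other than that baseline resistance, so that no patient is both excluded and scored as a failure. Keep the present exclusions as a sensitivity analysis.

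The cost is mainly wording, plus an amendment to the ethics bodies. Visits at 6 and 12 months are already scheduled and home tracing is part of routine care. No clinical management changes. Reported success rates may be somewhat lower.
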